Sexual dysfunctions can be treated effectively with face-to-face forms of sex therapy [38-41]. Sex therapy typically comprises a flexible treatment program including a number of elements that can be tailored to the needs of individuals and couples. It typically involves behavioral components derived from the sex therapy developed by Masters and Johnson [42], i.e. psycho-education about sexuality and sexual dysfunction, a temporary ban on intercourse, and sensate focus exercises. A ban on intercourse can break the vicious cycle of fear of sexual intercourse and subsequent negative experience and disappointment, and offers the opportunity for positive experiences by eliminating or reducing performance demand [43]. Sensate focus exercises form a hierarchically structured exercise program, through which partners gradually reintroduce the consecutive phases of sexual contact. The exercises are targeted at becoming more comfortable with one’s own body and achieving sexual intimacy with one’s partner, both physically and emotionally. Other goals are to discover new approaches to sexual stimulation, and to encourage communication between partners about sexual experiences, sexual desires and sexual boundaries. These behavioral elements of sex therapy are usually combined with cognitive therapy [40,43]. Through cognitive therapy, therapist and client aim to detect and modify the client’s dysfunctional, disturbing cognitions regarding sexuality that arise during exercises. Via the method of cognitive restructuring, the dysfunctional cognitions are replaced by more functional appraisals. Sex therapy is often delivered in a couple format, but individual applications and group therapy formats are also described in the literature [44,45].

The efficacy of different types of face-to-face therapy for female sexual dysfunction (FSD) has been demonstrated, including sexual desire and sexual arousal disorder [40,46,47], orgasmic disorder [48,49], sexual pain [50,51], and vaginismus [52,53]. Several modified treatment programs have been developed and evaluated for breast cancer survivors [44,54]. Interventions with stronger effects tend to be couple-focused and include treatment components that educate both partners about the woman’s diagnosis and treatment, promote couples’ mutual coping and support processes, and include treatment components that make use of specific sex therapy techniques addressing sexual and body image concerns [44,54].

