### Study sample

The study sample will be composed of 160 women fulfilling the following inclusion criteria: (1) age 18-65 years (the upper limit of 65 years is not based on any assumption regarding the salience of sexuality with increasing age, but on the smaller chance of access to internet in this age group); (2) a history of histologically confirmed breast cancer (stages: T1-T4, N0-N1 and M0); (3) a diagnosis of breast cancer six months to five years prior to study entry; (4) completion of breast cancer treatment (with the exception of endocrine therapy and immunotherapy); (5) disease-free at time of study entry; (6) a basic fluency in the Dutch language (for assessment and therapy purposes); and (7) a formal diagnosis of sexual dysfunction according to the criteria of the Diagnostic and Statistical Manual of Mental Disorders-IV [82] (to be established by an experienced sexologist during an intake interview). Single as well as partnered women can participate in the study. Sexual orientation is irrelevant for eligibility.

Exclusion criteria are: (1) no access to internet; (2) serious cognitive or psychiatric problems (i.e., depression, alcohol dependency, or psychotic disorders) as determined on the basis of the Mini International Neuropsychiatric Interview [83]; (3) treatment for another type of cancer (with the exception of cervix carcinoma in situ and basal cell carcinoma); (4) presence of severe relationship problems for which the internet-based program is not appropriate; (5) participation in a concurrent therapy program to alleviate problems with sexuality or intimacy; (6) participation in a concurrent CBT program for other psychological problems; and (7) participation in another trial investigating problems with sexuality/intimacy.

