### Study arms

#### Intervention group: internet-based CBT program

Each woman is assigned a sexologist who guides her through the internet-based CBT program. Contact with the therapist is web-based, via a secured, password-protected website. From a total of 10 modules, the sexologist selects four to five modules that best fit the sexual problems of the client. The internet-based CBT program was originally developed for use in the general population at Virenze, a mental health center located in Utrecht, the Netherlands. The program was adapted for use specifically for breast cancer survivors. This involved editing and adding text related to the physical and psychosexual problems often experienced by women who have had breast cancer. The therapists are licensed psychologists and sexologists who have undergone additional training in issues relating to breast cancer, and in the use of the internet program.

A description of the content of the different program modules is provided in Table 1. Each module contains several interventions, each of which comprises the following elements: (1) introduction, (2) psycho-education, (3) “homework” assignments (e.g., registration exercises; discuss intimacy with partner; sensate focus exercises) and (4) reporting back to the therapist and receiving feedback on the homework assignments. The modules can be used in varying order, leading to a tailored and flexible treatment program consisting of a maximum of 20 therapy sessions that are completed within a period of 24 weeks. A minimum of five sessions is considered the lower limit of sessions required in order to expect an effect. The average time investment for a participant is 90-120 minutes per week. Women are motivated by the sexologist to involve their partner in the treatment, but partner involvement is not mandatory. The time limit within which the therapist should respond to incoming messages from a client is set at five working days. Weekly contact between therapist and client is pursued. After 10 weeks of treatment, a mid-term evaluation is held to reflect on the progress so far, and to adjust goals, if necessary, for the remaining part of treatment. The internet-based CBT program is provided at no cost to the woman.

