#### Partners

Only partners of the women in the intervention group are asked to complete questionnaires regarding problems with sexuality and intimacy (male partner: IIEF [85], female partner: FSFI [86]), and relational functioning (PAIR Inventory [87], MMQ [84]) at the same points in time as the participants.

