### Statistical issues

#### Power calculation

The SAQ, FSFI, FSDS-R and PAIR Inventory are the primary outcome measures on which sample size calculations are based. With a total sample of 130 women (65 per group), and under the assumption of no interaction, the study will have a 80% power to detect a 0.5 standard deviation difference (Cohen’s effect size [98]) for the main effects of the internet-based CBT program, with the p-value set at 0.05 (two-sided test). A 0.5 standard deviation difference is considered to be indicative of clinically meaningful differences in self-reported symptom experience [98].

We will recruit 160 women into the study, to allow for an attrition rate of approximately 20% (i.e., women who discontinue participation in the study entirely, including failure to complete all follow-up questionnaires). Those women who discontinue the therapy but complete the follow-up assessments will be included in the intention-to-treat analysis.

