#### Statistical analysis

First, student’s t-tests or appropriate non-parametric statistics will be used to evaluate the comparability of the intervention and control group at baseline in terms of sociodemographic and clinical characteristics. If, despite the stratified randomization procedure, the groups are not comparable on one or more background variables, those variables will be employed routinely as covariates in subsequent analyses.

Questionnaire scores will be calculated according to published scoring algorithms. Between-group differences over time in mean scores will be tested using multilevel analysis. Effect sizes will be calculated using standard statistical procedures. All analyses will, to as great an extent as possible, be conducted on an intention-to-treat basis. Per protocol analyses will also be carried out (as a secondary analysis), comparing women who meet minimal compliance levels with the program with the control group. We will use correlation analyses to examine the relationship between degree of program adherence, partner involvement, and program effect. For the analysis of the secondary outcome measures, appropriate statistical (p value) adjustments will be made for multiple testing. The semi-structured interview data will be transcribed and content analyzed to extract narrative, qualitative information about the women’s experience with the intervention.

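### The planned raw correlation of partner involvement with program effect is open to confounding by baseline relationship quality, and among treated women the outcome can only be each woman's own change

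*Protocol article*

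**What the plan says.** The protocol article's Statistical analysis section gives one analysis that uses partner involvement: "We will use correlation analyses to examine the relationship between degree of program adherence, partner involvement, and program effect". It names no covariates for this analysis.

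Four other statements determine what such a correlation can mean:

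- Involvement is a choice made during treatment (Intervention group: internet-based CBT program): "Women are motivated by the sexologist to involve their partner in the treatment, but partner involvement is not mandatory".
- Partner data exist on one side of the trial only (Partners): "Only partners of the women in the intervention group are asked to complete questionnaires regarding problems with sexuality and intimacy".
- Women without a partner are eligible (Study sample): "Single as well as partnered women can participate in the study".
- The range of relationship quality is narrowed by an exclusion criterion (Study sample): "presence of severe relationship problems for which the internet-based program is not appropriate". Under Recruitment and randomization, an MMQ marital adjustment score above 35 leads to a renewed eligibility discussion, not to automatic exclusion. Table 2 gives the scale's range as 0 to 80.

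The efficacy question is handled separately, in the randomized groups: "Between-group differences over time in mean scores will be tested using multilevel analysis".

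**The concern.** An effect of the program is a contrast between arms. Adherence and partner involvement exist only among women who receive the program, so the correlation is in practice confined to the intervention arm, although the article does not say so. There, the only quantity available for each woman is her own change from baseline, which mixes the therapy's contribution with natural course and prognosis. Calling it *program effect* claims more than it can show.

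Involvement is also self-selected. Relationship quality at baseline is a plausible common cause: it may make a woman more likely to bring her partner in and, independently, more likely to improve. A raw correlation would credit that shared cause to involvement. The direction may also be reversed, if women who are improving involve the partner more as therapy proceeds.

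At stake is the interpretation of an exploratory result on a topic the article treats as relevant. Its Background reports of earlier work that "Interventions with stronger effects tend to be couple-focused", and the sexologists encourage partners to take part. A positive raw correlation could easily be taken as support for that practice.

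**Working it through.** **Inputs from the protocol article.** Evaluable women: 65 per group (Power calculation). Test level: two-sided 0.05 (Power calculation). The article states no level for the correlation, so the same one is assumed.

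**The plan's own figure.** The article states no figure for the correlation. The design figure from which the 65 comes does reproduce: "With a total sample of 130 women (65 per group), and under the assumption of no interaction, the study will have a 80% power" for a 0.5 SD difference. With the normal approximation, 0.5 × √(65/2) = 2.850; 2.850 − 1.960 = 0.890; power = Φ(0.890) = 81.3%. The t-test gives 80.8%.

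**Assumptions not in the article.** Involvement has no true effect on change. Baseline relationship quality Q correlates *a* with involvement and *b* with change, with *a* = *b* = 0.3, 0.4 or 0.5.

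**Step 1: spurious correlation.** If Q is the only link, the expected correlation is r = a × b:

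- 0.3 × 0.3 = 0.09
- 0.4 × 0.4 = 0.16
- 0.5 × 0.5 = 0.25

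**Step 2: how often it is significant.** By Fisher's z with n = 65, the test statistic has mean atanh(r) × √(n − 3) = atanh(r) × √62 = atanh(r) × 7.874 and SD 1. The rejection rate is P(Z > 1.96 − mean) + P(Z < −1.96 − mean).

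| a = b | r | mean | rejection rate, Fisher z | simulation, 5000 runs |
|---|---|---|---|---|
| 0 | 0 | 0 | 5% | – |
| 0.3 | 0.09 | 0.711 | 11.0% | 10.7% |
| 0.4 | 0.16 | 1.271 | 24.6% | 25.9% |
| 0.5 | 0.25 | 2.011 | 52.0% | 53.3% |

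**Step 3: other sample sizes.** In a separate simulation, 65 to 80 women were treated, of whom an assumed 0 to 30% were single and left out. The rate was 9 to 13% at 0.3 and 39 to 61% at 0.5.

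**Step 4: effect of adjustment.** In the same simulations, the partial correlation given Q rejected about 4 to 6% of the time in every scenario. That holds when Q itself is measured. With a proxy of reliability 0.88 (the upper Cronbach's alpha for MMQ marital adjustment in Table 2, taken here as the reliability) and a = b = 0.5, the squared correlation of the proxy with each variable is 0.25 × 0.88 = 0.22. The partial correlation is then (0.25 − 0.22)/(1 − 0.22) = 0.04, down from 0.25. Most of the confounding through this one variable is removed, but not all.

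**The case against.** The strongest reply is that the article promises only to examine a relationship. None of its hypotheses concerns partners, no decision hangs on this correlation, and efficacy rests on the intention-to-treat multilevel comparison. All of that stands. A reader might infer that the trial will judge the partner's role, or advise on partner participation, from this result. The text does not say so. The Background sentence on couple-focused interventions summarizes earlier literature and goes on to list other treatment components.

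A second reply is that the size is assumed. That stands too: the article gives no correlation between relationship quality and involvement or change, and with none the rate is about 5%. Excluding severe relationship problems and reviewing high MMQ scores narrows the confounder by an unknown amount. It does not remove it.

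A reader might also infer that single women will be counted as having low involvement, which could create an association by itself. No sentence codes them that way. If they are left out, this source adds no bias and costs only sample size. The coding may be settled in the full protocol or analysis plan, which is not shown.

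Finally, one might want to answer the partner question from the randomized data, through arm × relational status or arm × baseline relationship quality. Those terms show who benefits, not whether involving the partner helps, because involvement was not randomized. The first is also very imprecise. With an assumed 15% single, each arm of 65 has 9.75 single and 55.25 partnered women, so the interaction's standard error is √(2/9.75 + 2/55.25) = 0.49 SD and its 95% interval about ±0.96 SD. The design effect is 0.5 SD.

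What the replies leave standing is narrower. The article does fix the method, a correlation with no adjustment named, and the label *program effect*. A better method is available from data already collected.

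**Conclusion.** The point holds in a limited form and is of low severity. As written, the correlation cannot separate a benefit of involving the partner from better change among women in better relationships, and its outcome is wrongly labelled. With no true effect of involvement and shared-cause correlations of 0.3, 0.4 or 0.5, about 11%, 25% or 52% of trials with 65 treated women would show a significant association. These figures illustrate how sensitive the analysis is. They do not predict this trial's result, and they depend entirely on the assumed confounding.

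The documents do not support the stronger conclusion that the plan will declare a partner benefit or that its treatment of single women is wrong. The sample size and the primary intention-to-treat comparison are unaffected. The same reasoning bears on adherence, named in the same sentence, but this point is confined to partner involvement.

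**What to change.** In the Statistical analysis section, for partner involvement:

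- Replace the raw correlation with a regression or partial correlation in partnered women of the intervention arm, adjusted for the T0 score of the outcome concerned and T0 MMQ marital adjustment.
- Call the outcome change in treated women, not program effect.
- Report the estimate with a confidence interval, as exploratory and non-causal.

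Arm × baseline relationship terms in the multilevel model are optional. If used, report them as estimates with intervals on who benefits, not as a replacement for this analysis.

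The cost is a few words and two covariates. The baseline questionnaire already covers the study outcomes, and the MMQ marital score is already used there to check eligibility. The downsides are a somewhat smaller n once single women are left out, and residual confounding through measurement error, unmeasured causes and reverse direction. The non-causal label is therefore needed even after adjustment.

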**Primary outcomes**		
Sexual functioning	SAQ [88,89]	• Assesses sexual functioning
		• 10 items; 4-point Likert scales
		• Subscales: pleasure; discomfort; habit
		• Subscale scores: pleasure 0-18; discomfort 0-6; habit 0-3; higher score indicates higher levels of pleasure; lower score indicates lower levels of discomfort; habit is a single item (0 ‘less sexual activity than usual’ to 3 ‘much more sexual activity than usual’)
		• Time frame: past month
		• Test retest kappa: 0.50-0.76
	FSFI [86,90]	• Assesses sexual functioning
		• 19 items; 5- and 6-point Likert scales
		• Subscales: desire; arousal; lubrication; orgasm; satisfaction; pain
		• Total score*: 2-36/Subscale scores*: desire 1.2-6; arousal 0-6; lubrication 0-6; orgasm 0-6; satisfaction 0.8-6; pain 0-6; higher score indicates better sexual functioning
		• Time frame: past 4 weeks
		• Cronbach’s alpha: >0.82
	FSDS-R [91,99]	• Assesses distress related to sexual dysfunction
		• 13 items; 5-point Likert scale (0 ‘never’ to 4 ‘always’)
		• Total score: 0-52; higher score indicates higher level of sexual distress
		• Time frame: past 30 days
		• Cronbach’s alpha: >0.88
Intimacy	PAIR Inventory [87]	• 36 items; 5-point Likert scale (0 ‘strongly disagree’ to 4 ‘strongly agree’)
		• Subscales: emotional intimacy; social intimacy; sexual intimacy; intellectual intimacy; recreational intimacy; conventionality
		• Subscale score*: 0-96; higher score indicates higher levels of intimacy
		• Time frame: ‘how the relationship is now’
		• Cronbach’s alpha: 0.70-0.80

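### Four instruments are co-primary with no lead score or success rule, and multiplicity adjustment is stated only for the secondary outcomes, so the 5% error rate and the 80% power cannot both hold for the primary claim

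*Protocol article*

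**What the plan says.** The power paragraph states: "The SAQ, FSFI, FSDS-R and PAIR Inventory are the primary outcome measures on which sample size calculations are based". The Outcome measures section and Table 2 list the same four. None of these places gives a lead instrument, a composite or an order of testing. The power paragraph claims 80% power for a 0.5 SD difference with 65 women per group, using a two-sided p-value of 0.05 that is not divided over the four.

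Table 2 lists these scores for the four primary instruments:

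- SAQ: "Subscales: pleasure; discomfort; habit", with no total given.
- FSFI: "Subscales: desire; arousal; lubrication; orgasm; satisfaction; pain", plus a total ("Total score*: 2-36/Subscale scores*: desire 1.2-6").
- FSDS-R: one score ("Total score: 0-52; higher score indicates higher level of sexual distress").
- PAIR: "Subscales: emotional intimacy; social intimacy; sexual intimacy; intellectual intimacy; recreational intimacy; conventionality", with no total given.

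The Statistical analysis section says that between-group differences over time will be tested by multilevel analysis. On multiplicity it says: "For the analysis of the secondary outcome measures, appropriate statistical (p value) adjustments will be made for multiple testing". It says nothing comparable about the primary measures. The primary hypothesis, at the end of the Background, is greater improvement in sexual functioning and intimacy. It does not say how many measures must show this.

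**The concern.** The outcomes that carry the efficacy claim have less stated protection against chance findings than the supportive ones. Four co-equal primary measures at an undivided 0.05 have a joint error rate of 5% or less only if success requires all of them, and the article states no such rule. Without a rule, a mixed result (for example FSDS-R positive, PAIR and SAQ not) has no interpretation fixed in advance, and a single chance finding could be reported as confirming the hypothesis.

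The stated power is tied to the same gap. It is the power of one test at 0.05, and most ways of controlling error over four measures change it. For SAQ and PAIR, even one test per instrument is undefined, because Table 2 lists subscales and no total.

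**Working it through.** **Inputs from the protocol article.** Four primary instruments, 65 per group, effect 0.5 SD, two-sided 0.05, 80% power (Power calculation). Scores per instrument: 3 + 7 + 1 + 6 = 17 (Table 2).

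**Assumption.** The article gives no correlations between instruments. A common correlation r is assumed and varied.

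**1. The plan's own figure.** The expected z is 0.5 × √(65/2) = 2.850. Power at two-sided 0.05 is Φ(2.850 − 1.960) = 0.813; the noncentral t gives 0.808. The stated 80% is reproduced, for one test.

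**2. Error if any one positive result suffices, each test at 0.05.** For independent tests the chance of at least one false positive among k is 1 − 0.95^k, so for four it is 1 − 0.95⁴ = 0.185. For correlated tests, z_j = √r·C + √(1−r)·E_j was simulated with C and E_j standard normal (1,000,000 draws), counting draws with any |z_j| > 1.96.

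| Assumed r | 4 tests (one score per instrument) | 17 tests (all listed scores) |
|---|---|---|
| 0 | 18.5% | not usable, see step 3 |
| 0.3 | 17.4% | 49.3% |
| 0.5 | 15.6% | 38.6% |
| 0.7 | 13.0% | 27.0% |
| 0.9 | 9.4% | 14.9% |

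Every entry is above 5%.

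**3. Why independence is not usable for 17 scores.** Table 2's own ranges show that the FSFI total is the sum of its six domains. The minima add to 1.2 + 0 + 0 + 0 + 0.8 + 0 = 2 and the maxima to 6 × 6 = 36, which are the limits of the total. These scores cannot be independent.

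**4. Power if all four must be significant.** Each z has mean 2.850 (0.5 SD on every instrument) and all four must exceed 1.96. Simulated power is 0.44, 0.52, 0.58 and 0.64 at r = 0, 0.3, 0.5 and 0.7.

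**5. Power if error is controlled another way, at 65 per group.**

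- Fixed sequence: the first test keeps 0.05, so its power is 0.81.
- Plain Bonferroni, 0.05/4 = 0.0125: for any single pre-named outcome, Φ(2.850 − 2.498) = 0.638; the noncentral t gives 0.625.
- Holm, with 0.5 SD on all four: average power per outcome is about 70 to 75% over r = 0.9 to 0. The chance that the smallest of the four p-values falls below 0.0125 is a different quantity, about 76 to 98% over the same range. The 62% must therefore not be quoted as the power of the smallest p-value.

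**The case against.** The strongest defence is that this is a condensed article and that the full protocol or SAP may set the primary testing rule. Silence alone would then be no finding. But the article is not silent. It makes a choice on multiplicity, assigns it to the secondary outcomes, and sizes the primaries at an undivided 0.05. If an unseen document controls error over the four, the 80% stands only for the first test of a fixed sequence and otherwise needs restating. If it does not, the inflation stands.

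A second defence is that the hypothesis joins sexual functioning and intimacy, so both might be required. That is a fair reading, but the text does not make it a decision rule. Requiring all four instruments would also lower the power, as shown in step 4.

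Several stronger readings are tempting, and the article does not support them:

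- **Each primary outcome is tested at 0.05.** This is inferred from the power paragraph and the secondary-only adjustment. The analysis section gives no test level for the primaries.
- **One significant score is enough.** The article states neither this nor its opposite. The defect is that the rule is missing.
- **There are 17 primary tests.** Table 2 describes the scoring of every instrument, primary and secondary. It does not declare each subscale a primary test, so 17 is an upper bound.
- **The error rate is 58%.** That is 1 − 0.95¹⁷, which needs the independence ruled out in step 3.
- **Separate tests at T1 and T2 multiply the count further.** The analysis section describes a multilevel analysis of differences over time, not one test per visit.

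**Conclusion.** The point holds for the four named instruments. With one score each tested at 0.05 and any positive result counting, the chance of at least one false-positive primary result is about 13 to 17% at assumed correlations of 0.7 to 0.3, with 18.5% under independence and about 9% at 0.9. If all listed scores were tested, the corresponding upper bound is about 27 to 49% at correlations of 0.7 to 0.3. If all four instruments must succeed, error is at most 5%, but power is about 44 to 64% at correlations of 0 to 0.7.

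None of these readings gives both a 5% error rate and 80% power for a claim resting on four co-equal measures. The size depends on the assumed correlations and on which success rule was meant. The direction does not: every any-one-positive scenario examined exceeds 5%, and every all-four scenario examined falls short of 80%.

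**What to change.** Before outcome data are seen, change the Statistical issues section as follows:

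1. Name one score for each of SAQ, FSFI, FSDS-R and PAIR, and the primary contrast or time point.
2. State one family-wise procedure over these four: a fixed sequence, Holm, or a rule that all must succeed. The choice, and the order in a sequence, is for the trial team; the article does not dictate it.
3. Place the remaining subscales of these instruments in the secondary family that is already to be adjusted.
4. Restate power to match: about 80% for the first test of a fixed sequence; about 70 to 75% on average per outcome under Holm if all four effects are 0.5 SD; about 62% for any single pre-named outcome under plain Bonferroni; about 44 to 64% if all four must succeed.

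The cost is wording and a restated power figure, with no extra patients or data. The downside is that outcomes late in a sequence, or individual outcomes under Holm or Bonferroni, become harder to declare positive.
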